### Interventions

Patients will be receiving twice a day tDCS (applied current at 2mA) or sham stimulation, for 3 weeks on working days (30 sessions in total). Each stimulation will last 25 minutes and take place at a two-hour interval. The detailed schedule of meetings and measurement methods is presented in **Table 1**.

**Table 1 T1:** Schedule of enrolment, interventions, and assessments.

	Study Period				
	Enrolment	Baseline	Intervention period (tDCS stimulations)	End of the intervention period	Safety Follow-up
Timepoint (day)	-2 to -1	0	1-21 ( ± 1 days)	22 ( ± 1 days)	35 ( ± 7 days)
Visit number	V0	V1		V2	V3
Eligibility screen	X				
Informed consent	X				
Sociodemographic data	X				
Randomization		X			
ASSESSMENTS:					
Weight	X	X	X	X	X
Performing body composition analysis		X		X	X
Psychological		X		X	
Neuropsychological		X		X	
Dietary behaviors and nutrition		X		X	X
Biological	X	X	X	X	
Adverse events	X	X	X	X	X

Participants in the active tDCS group will receive active stimulation to DLPFC via two saline-soaked, 25 cm2 (5 cm x 5 cm) sponges saline-soaked placed over F3 (anode) and F4 (cathode), according to the International 10–20 system. The electrodes will be placed on the patient’s head using a specially designed headband. The patient’s skin should be clean and dry. Each time, it will be checked whether the skin has any wounds, irritations, or other dermatological issues that could affect the safety and comfort of the patient.

In the sham tDCS condition, an identical protocol was employed. When the system is programmed as Sham, the device will ramp up to the programmed intensity and then back down to a test current of 25 microamps. It will stay at this test current to make sure the contact quality measurement is correct for the remainder of the session and then will ramp up to the programmed intensity and then back down to the test current at the end of the session. The system will ramp up for 30 seconds and back down for 30 seconds at the beginning and the end of each session for Sham stimulation. For Active stimulation, there is an initial ramp up of 30 seconds to the programmed intensity and then at the end of the session, the current ramp down to test current in 30 seconds. The commercially available Soterix Medical Inc. 1x1 tDCS mini-CT LTE device (model 1601-LTE) will be used for stimulation. The first stimulation will take place after obtaining the patient’s written consent, completing questionnaires, performing body composition analysis, EEG and blood tests. The stimulation device will always be triggered by one of the team members. During the stimulation, the patient can move freely and will be encouraged to do activities that additionally stimulate the brain, such as reading, solving crosswords or engaging in conversation. During the school year, simulations will take place during lessons conducted at the hospital. All patients will additionally receive treatment-as-usual, including nutritional rehabilitation, individual and family psychotherapy, psycheducation, and (if necessary) pharmacotherapy.

### Measures

To verify the effectiveness of both the active and sham tDCS stimulation methods, the following measures will be used:

I. For sociodemographic data: self-prepared personal questionnaire. The survey will cover personal data, medical history, information on menstruation, and used pharmacotherapy.

II. For psychological data:

The psychological examination consists of 14 tests using the paper-and-pencil method and is divided into 2 parts (the minimum interval between their administration is 4 hours, presented in the **Table 2**). During this time between examinations, patients were hospitalized in the ward. The psychological diagnosis will examine the following areas: neurocognitive functions (complex attention, executive functions, memory, language, social cognition), mood, obsessive-compulsive symptoms, and stress levels and assessment of early childhood injuries related to the experience of abuse, emotional, bodily, sexual, emotional, and physical neglect, and level of satisfaction with one’s own body. The first part includes the following tools: The Rey-Osterrieth complex figure test (ROCF), The Children’s Depression Inventory 2 (CDI-2)/the Beck Depression Inventory (BDI), The Yale-Brown Obsessive Compulsive Scale (CY-BOCS), The Color Connection Test (CTT1 and CTT2), The Benton Visual Retention Test (BVRT), The Perceived Stress Scale (PSS-10), The Childhood Trauma Questionnaire (CTQ) (30- 45 minutes); the second part includes: The Ruminance-Reflectivity Questionnaire (RRQ), The Attention and Perceptiveness Tests (APT), The Appearance Self-Rating Sheet (ASRS), The Verbal Fluency Test (VFT), The Metacognition Questionnaire (MCQ-A) (30- 45 minutes) measure for V1 and V2 respectively.

**Table 2 T2:** List of psychological tests performed on patients with AN.

Part 1	Part 2
1. The Rey-Osterrieth complex figure test 2. The Children’s Depression Inventory 2/Beck Depression Inventory 3. The Yale-Brown Obsessive Compulsive Scale 4. The Color Connection Test 5. The Benton Visual Retention Test 6. The Perceived Stress Scale 7. The Childhood Trauma Questionnaire	1. The Matching Familiar Figures Test 2. The Attention and Perceptiveness Tests 3. The Verbal Fluency Test 4. The Appearance Self-Rating Sheet 5. The Metacognition Questionnaire 6. The Ruminance-Reflectivity Questionnaire

1) The Beck Depression Inventory (BDI) by Aaron Beck- It is a self-assessment tool that is helpful in screening the diagnosis of depression and measuring its severity (31). It consists of 21 multiple-choice questions. This tool will be used for adolescents who are over 18 years of age. The Polish adaptation was validated by Zawdzki, Popiel & Pragłowska. Cronbach’s alpha was 0.930 and 0.950, respectively (32);2) The Children’s Depression Inventory 2 (CDI2) by Maria Kovacs. A set of questionnaires is responsible for the self-reporting measurement of the severity of symptoms of depression in children and adolescents. It consists of 28 questions, the respondent chooses the answer containing the mode of functioning closest to his or her well-being. The filling time is 10-15 minutes. The test is intended for children aged 7-18 (33). The Polish adaptation was validated by Wrocławska-Warchala, Wujcik & Kovacs was used. Reliability for the general Cronbach’s α score is 0.840–0.870 (34);3) The Metacognition Questionnaire (MCQ-A) by Cartwright-Hatton, Mather, Illingworth, Brocki, Harrington, & Wells - is a reliable and valid instrument for assessing the severity of dysfunctional metacognitive beliefs in adolescents (aged 12-18) that affect their daily functioning (35). The first and second subscales measure “positive and negative beliefs about worry,” Subscale 3 measures “cognitive confidence,” and Subscale 4 measures “beliefs about superstition, punishment, and responsibility”. Finally, subscale 5 measures “cognitive self-consciousness,”. The test takes 10-15 minutes. The Polish adaptation were validated by Kajka & Kulik was used. Cronbach’s alpha reliability analysis for the adapted questionnaire was 0.874 (36);4) The Perceived Stress Scale (PSS-10) by Cohen, Kamarck & Mermelstein. Consists of 10 questions and is used to measure stress based on subjective feelings related to problems and personal events, behavior, and coping with stress (37). On average, completing the test takes up to 5 minutes. The questionnaire has age norms for youth 18 years and older. The Polish adaptation was validated by Juczyński i Ogińska-Bulik. Cronbach’s alpha reliability analysis for the adapted questionnaire was 0.860 (38);5) The Childhood Trauma Questionnaire (CTQ) by Bernstein, Fink, Handelsman & Foote. CTQ is used to assess early childhood injuries related to the experience of abuse, emotional, bodily, sexual, emotional and physical neglect. The questionnaire has age norms for adolescents (aged 12-17). Cronbach’s alpha reliability analysis for this questionnaire was 0.900 (39). The Polish translation was done by Murzyn (40);6) The Attention and Perceptiveness Tests (APT) version 6/9- Performing the test consists in drawing the given symbols - 6, 9 among other similar ones within three minutes. The questionnaire has age norms for youth from 14 to 18 and adults over 18 years of age. The reliability of this tool measured as temporal consistency (test-retest) is 0.790. On average, completing the test takes 3 minutes. The author of the tool is Ciechanowicz (41);7) The Rey-Osterrieth complex figure test (ROCF) was first designed by Rey and then standardized by Osterrieth. This is a neuropsychological test extensively used to investigate visuospatial constructional functions, visual graphic memory, and some aspects of planning and executive function. The questionnaire has age norms for children and adolescents from 8.6 years to 13.6 years. Cronbach’s alpha reliability analysis for this questionnaire was 0.761-0.793 (42). In the present study, participants first recreate the pattern patterns from the cards, then have a break to complete another questionnaire (CTT), and then recreate the patterns from memory after the break time (43);8) The Yale-Brown Obsessive Compulsive Scale (CY-BOCS) by Goodman, Price, Rasmussen, Mazure, Fleischmann, Hill, Heninger, & Charney is a scale designed to measure the severity and type of symptoms in people with obsessive-compulsive disorder (44). The respondents answer 10 questions about the occurrence of symptoms in the last week. The questionnaire has age norms for children and adolescents from 12 years to 16 years. The Polish adaptation was validated by Bryńska & Wolańczyk. Cronbach’s alpha reliability analysis for this questionnaire was 0.810 (45);9) The Colour Connection Test (CTT-1, CTT-2) by D’Elia, Satz, Uchiyama, & White. The Neuropsychological Point Matching Test measures attention, executive function, and psychomotor skills (28). It consists of connecting points with straight lines according to specific rules. The test takes 4 minutes. The Polish adaptation were validated by Łojek & Stańczak. The questionnaire has age norms for children and adolescents from 6 years to 80 years. Cronbach’s alpha reliability analysis for this questionnaire was 0.600-0.900 (46, 47);10) The Benton Visual Retention Test (BVRT) by Benton is used to test memory, visual perception and graphomotor skills. The examined person draws the presented patterns (10 pieces) from memory or redraws them, depending on the version and methods of the research carried out by the researcher. The questionnaire has age norms for children and adolescents from 8 years to 69 years (48). Testing one version takes about 5 minutes. The Polish adaptation was validated by Jaworowska, Bac & Stańczak. The analysis of reliability as the consistency of judges’ ratings was assessed as very high (0.900-0.970) (49);11) The Appearance Self-Rating Sheet (ASRS) - Sheet is a tool to measure the Assessment of 25 dimensions related to your body - (different parts of your body). The patient receives a visualization of the body figure on the drawing and evaluates its individual elements. The test allows you to assess the importance of appearance for patients, the assessment of satisfaction with one’s appearance, and the satisfaction index. The questionnaire has age norms for people aged 17-47. The authors of the test are Janowski, Staniewski & Jedynak. Cronbach’s alpha reliability analysis for this questionnaire was 0.719 (50).12) The Ruminance-Reflectivity Questionnaire (RRQ) by Trapnell & Campbell *i*s a tool used to measure the intensity of processes of rumination (and reflectivity) (51). The Polish adaptation of the tool consists of 12 questions, to which the respondent responds on a 5-point scale, where 1 means - I do not agree completely, and 5 - I agree completely. The questionnaire has age norms for people aged 20-50. Cronbach’s alpha reliability analysis for this questionnaire was 0.900-0.910. The author of the test is Radoń (52);13) The Verbal Fluency Test (VFT) by Thurstone allows for analyzing the number of spoken words beginning with the letter chosen. In the Polish version, the respondent has to enumerate as many words for the K letter as possible in 60 seconds. This is a clinical experimental test used in the diagnosis of both children and adults. Polish standards are for children aged 10-12. Reliability as temporal consistency of this tool is high, and it corresponds to a correlation coefficient of over 0.700. The Polish adaptation were validated by Borkowska, Sajewicz-Radke, Lipowska & Kalka (53);14) Matching Familiar Figures Test (MFF) by Kagan, Rosman, Day, Albert & Phillips is used to measure conceptual tempo, that is, the relative speed with which an individual makes decisions on complex tasks (see reflection – impulsivity). It consists of the fact that the examined person has a drawing presented, and then from among 6 pictures, he has to choose the one he saw previously. The researcher counts the time in which the decision was made (54). The Polish adaptation was validated by Matczak & Wujcik. The questionnaire has age norms for people aged 9-17. Reliability analysis for reaction time showed a high index (0.85 - 0.90) and a low index for the number of errors (0.400 - 0.580) (55).

III. For assessing dietary behaviors and nutrition outcomes:

Dietary diagnosis includes 4 tests covering issues related to the severity of symptoms of eating disorders, habits and nutritional knowledge. The patient completes the questionnaires by hand, and the examination takes up to 30 minutes.

1) Eating Attitudes Test (EAT-26)- Standardized test for the detection of symptoms of eating disorders (56). It is used for screening the population at risk of anorexia, bulimia and obesity. In addition to the global score, it is also possible to analyze three EAT-26 domains, such as: (1) dietary behavior, (2) bulimia & food preoccupation, (3) oral control. The measure can be used with adolescents (13+) and adults. The EAT-26 has demonstrated good to excellent internal consistency, ranging from 0.86–0.90. Polish adaptation: Rogoza, Brytek-Matera & Garner (57);2) Questionnaire Eating Behaviors (QEB)- The qualitative questionnaire is designed to study eating habits and opinions about food and nutrition. The first part of the questionnaire covers the frequency of consumption of selected products, the frequency of eating meals and their typical composition. In the second part of the questionnaire, there are 26 statements about food and nutrition, which enable the assessment of the level of nutritional knowledge of the respondents. The questionnaire does not include age brackets. The Polish adaptation: Wądołowska and Krusińska (58);3) Food Intake Variety Questionnaire (FIVq)- The Variety Food Consumption Questionnaire is a qualitative food consumption frequency questionnaire. The questionnaire does not include age brackets. It is a simple tool to collect information on the consumption of (yes/no) 63 assortment groups of products. The authors of the test are Niedźwiedzka, Wądołowska (59);4) Eating Disorder examination questionnaire (EDE-Q 6.0) by Fairburn & Beglin. The questionnaire collects data on eating behavior for the past 28 days using subscales such as: restriction, eating-related anxiety, overeating. The questionnaire has been designed for adolescents aged 14 and older (60).

IV. Scale of adverse event monitoring:

To monitor the safety and tolerability of planned neurostimulation, the tDCS Side Effects Questionnaire by Brunoni et al. will be utilized (61). Although, the application of 2mA has been considered safe in the pediatric population (62) we intend to prioritize safety considerations and meticulously monitor for potential side effects. The questionnaire is designed to standardize and improve the way adverse events are reported in clinical trials using tDCS, aiming to enhance the understanding of the safety and tolerability of this method. The self-evaluation concerns the following twelve possible tDCS side effects (headache, neck pain, scalp pain, tingling, itching, burning sensation, skin redness, sleepiness, trouble concentrating, acute mood change, others), rating on 4-point Likert scales to which extent they had experienced them (from 1: “absent” to 4: “severe”), and to which extent they attributed each experienced side effect to tDCS (from 1: “not at all” to 4: “completely”). Participants will complete the questionnaire after each tDCS session and the follow-up.

V. For biological outcomes:

A venous blood sample (20 ml) after overnight fasting will be obtained from all participants. The standard laboratory tests (complete blood count: CBC, as a marker of nutritional status) will be run by the hospital laboratory. We will examine additional parameters that are influenced by nutritional status:

ferritin;thyroid stimulating hormone (TSH), free triiodothyronine (fT3), free thyroxine (fT4);phosphorus, magnesium and calcium;markers of food intake regulation (plasma leptin and serum visfatin).neurotrophins (serum brain-derived neurotrophic factor: BDNF, nerve growth factor: NGF, neurotrophin 3 and 4).marker of psychological stress: serum cortisol.

The part of the blood drawn will be centrifuged to obtain serum and plasma, pipette and frozen at -80°C for further analysis. All analyses will be performed via enzyme-linked immunosorbent assay (ELISA).

VI. For anthropometric data:

Body weight will be measured, and body composition will be analyzed using the electrical bioimpedance method (BIA). Measurements will be conducted three times at each stage of the study using the Impedimed device. During the examination, patients will be in a supine position with disposable electrodes placed on the left wrist and ankle of the left leg. The device scans 256 frequencies between 3 kHz and 1000 kHz and using Cole’s modeling with Hanai mixture theory, total body water, extracellular fluid, and intracellular fluid are determined. From there, fat-free mass and fat mass are calculated on the device.

VII. Neurophysiological data:

The protocol implies two EEG assessments: before the first tDSC (V1) session and after the last tDCS session (V2). The EEG measurement will take place in a well-lit, quiet room prepared for EEG examinations. A 21 Ag/AgCl electrodes cap is placed on the subject’s head, and the electrodes are covered with a gel to improve electrical conductivity. Additionally, ear clip cup electrodes will be used. The cap is additionally tightened with an elastic belt. The recording is preceded by verifying the impedance which will be kept below 5 kΩ for all electrodes. A resting-state recording with eyes closed will be performed for 10-15 minutes. Both EEG evaluations will be conducted with the same equipment and procedure. The recording will include 10-20 system of electrodes displacement with a sampling frequency of 256 Hz. After recording, the data will be band-pass filtered from 4 to 45 Hz with an active notch filter set at 50 Hz. The data will be exported in ASCII format. In further steps, EEG re-coded files will be imported to EEGLAB (63) open-source toolbox for MATLAB (Mathworks, Inc). Recordings will be cleared from artifacts in two ways, first by visual inspection by certified clinical neurophysiologist, and second using ASR and ICA algorithms. A pre-set relative amplitude values will be set as theta (4-8Hz), low-alpha (8-10.5Hz), high alpha (10.5-13Hz), beta (13-30Hz), and gamma (30-45Hz). Time-frequency analysis will bring outcomes regarding dominant frequency band power and the measurement of each frequency amplitude. This analysis will be conducted using globally averaged recordings, and will consider both the left and right hemispheres, as well as anterior asymmetry. Next, to assess signal-based functional connectivity, a weighted phase lag index (wPLI) will be used due to its consistency at a specific time and frequency examined across a pair of electrodes that minimizes the impact of volume conduction (64). FC will be analyzed in each frequency individually, with regard to its global strength and variability.

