#### Secondary outcome measures

For the purpose of evaluating the effectiveness of tDCS in treating AN, a range of secondary outcome measures will also be utilized, defined as changes in: 1. anthropometric measurements (in this BMI), 2. brain bioelectric activity, 3. nutritional status, 4. mood, 5. neurocognitive functions (attention, memory, and some aspects of planning, verbal fluency, and another executive function), 6. psychological measurements connected with: dysfunctional metacognitive beliefs, other aspects related to thinking such as reflectivity, impulsivity, rumination, obsessive-compulsive symptoms, stress levels and assessment of early childhood injuries related to the experience of abuse, emotional, bodily, sexual, emotional, and physical neglect, and self-assessment of the appearance of one’s body, 7. selected biological markers related to stress, food intake, inflammation and neurotrophins.

As regards the neurophysiological measures, we expect that a series of the tDCS sessions will be associated with changes in three aspects: 1. reduction of lower frequencies (delta and theta) in the dominant frequency spectrogram accompanied with an increase in the power of alpha and beta frequencies, 2. modification of alpha anterior asymmetry patterns associated with affective functioning towards less right-hemisphere-oriented and more left-hemisphere oriented pattern, 3. changes in the strength and variability of functional connectivity, with particular alterations regarding alpha (increase) and beta (decrease) frequencies, what is associated with the ability to gain more relaxed and less tensive states recorded during resting-state condition. The neurophysiological examination will be conducted during the V1 and V2 meetings.

Secondary psychological outcome measures will be gathered during the initial assessment (V1) and V2, while nutritional data will be collected at V1, V2, and V3 after follow-up. Biological outcomes will be recorded at V1 and V2, with additional measurements of BMI and BIA analysis also at V3. Neurophysiological outcome measures will be obtained during V1 and V2.

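### The 4–45 Hz filter and the band list leave out delta, so the delta part of the first EEG expectation cannot be tested as written

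*Protocol article*

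**What the plan says.** Two parts of the Protocol article bear on this.

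- **Measures, VII. Neurophysiological data** fixes the processing. Resting EEG is recorded at V1 and V2, sampled at 256 Hz. The filter step that follows is worded thus: "the data will be band-pass filtered from 4 to 45 Hz with an active notch filter set at 50 Hz". Export comes next ("The data will be exported in ASCII format"), followed by import into EEGLAB, artefact removal and time-frequency analysis. The pre-set bands are "theta (4-8Hz), low-alpha (8-10.5Hz), high alpha (10.5-13Hz), beta (13-30Hz), and gamma (30-45Hz"; the list ends there and contains no delta band. The time-frequency analysis is to give the dominant frequency band power and the amplitude in each frequency.
- **Secondary outcome measures** lists brain bioelectric activity among seven secondary domains and states three EEG expectations. The first is a "reduction of lower frequencies (delta and theta) in the dominant frequency spectrogram accompanied with an increase in the power of alpha and beta frequencies". The second concerns alpha anterior asymmetry. The third concerns alpha and beta functional connectivity.

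The article gives no frequency limits for delta and describes no separate processing path that keeps content below 4 Hz.

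**The concern.** The expected change names delta, but the processing removes the range in which delta lies before any band is computed. This is not detail that a condensed article leaves to a fuller document. The filter, the bands and the expectation are all stated, and they cannot all stand together.

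At stake is how one secondary EEG result can be read. If the text stays as it is, a report that lower frequencies fell, or did not fall, would rest on theta alone while the pre-stated expectation covers delta too. A dominant-frequency result would also be confined to 4 Hz and above by construction, although this expectation is framed in terms of the dominant-frequency spectrogram.

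**Working it through.** **Inputs**

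- Pass band: 4 to 45 Hz (Measures, VII).
- Defined bands: theta 4–8, low-alpha 8–10.5, high alpha 10.5–13, beta 13–30, gamma 30–45 Hz (Measures, VII).
- Bands named in EEG expectation 1: delta, theta, alpha, beta (Secondary outcome measures).
- Delta range: not given. The upper limit of 4 Hz is inferred from the article's lower theta edge. A lower limit of 0.5 Hz is an assumption.

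**Step 1. Do the defined bands leave room for delta?** The band widths are 4 + 2.5 + 2.5 + 17 + 15 = 41 Hz, and the pass band is 45 − 4 = 41 Hz wide. The bands are contiguous and fill the pass band exactly.

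**Step 2. Overlap of delta with the pass band.** Overlap = max(0, min(4, 45) − max(0.5, 4)) = max(0, 4 − 4) = 0 Hz. The assumed lower limit does not matter: any lower limit below 4 Hz gives the same result.

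**Step 3. Could the filter's gradual roll-off leave a usable delta signal?** The article gives neither filter type nor order, so this is a sensitivity check under an assumed Butterworth 4–45 Hz filter at 256 Hz sampling. Attenuation is 20·log10|H(f)|. Retained power is the average of |H(f)|² over 0.5–4 Hz, either unweighted (flat spectrum) or weighted by 1/f.

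| Assumed order | 1 Hz | 2 Hz | 3 Hz | Power retained, flat | Power retained, 1/f |
|---|---|---|---|---|---|
| 2 | −25.5 dB | −13.4 dB | −6.7 dB | 14% | 7.5% |
| 4 | −50.9 dB | −26.3 dB | −11.6 dB | 7.7% | 3.7% |
| 8 | −101.8 dB | −52.6 dB | −22.6 dB | 4.1% | 1.8% |

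Even at order 2, the gentlest of the three, the share of power passed is 10^(−0.67) ≈ 21% at 3 Hz, 10^(−1.34) ≈ 4.6% at 2 Hz and 10^(−2.55) ≈ 0.3% at 1 Hz. What survives lies mostly just below the cut-off and depends on the filter design. It is not a measure of delta.

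**Step 4. Is anything else limiting delta?** Not the sampling rate: 256 Hz resolves frequencies up to 256/2 = 128 Hz. In the procedure as described, the limit comes from the 4 Hz cut-off and the band list.

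**Step 5. What remains testable?** Of the four components in expectation 1, theta, alpha and beta lie inside the pass band and have defined bands; delta does not. Expectations 2 and 3 name only alpha and beta. The mechanism stated with the primary outcome also refers only to alpha and beta.

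**The case against.** The strongest reply is that this is a small inconsistency. Delta appears once, in a parenthesis, in one of three EEG expectations within one of seven secondary domains. The filter is applied after recording, so delta may still be present in the raw files. All of that stands and limits the weight of the point. It does not remove the contradiction, because no other part of the article reconciles the two sections.

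A reader might infer more than the document supports:

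- **That the whole first expectation is untestable.** It is not. Three of its four components have defined bands inside the pass band.
- **That theta is compromised because its lower edge is the filter edge.** Attenuation near 4 Hz depends on a filter design that the article does not state. The article also says that both EEGs use the same equipment and procedure, so a fixed attenuation would apply alike at both visits and in both arms. No bias in the comparison of arms is shown.
- **That relative amplitudes are wrong because delta is missing from the denominator.** The article does not define the denominator. Normalising to the analysed range is a legitimate convention, and it keeps changes in delta from moving the relative alpha and beta values.
- **That delta data are lost.** The article does not say whether unfiltered files are kept or what the amplifier passes, so neither loss nor recoverability can be asserted.

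**Conclusion.** The point holds in a limited form. With theta starting at 4 Hz, a 4 Hz lower cut-off and no delta band, the delta component of EEG expectation 1 cannot be tested as written, and a dominant frequency below 4 Hz cannot be detected. This applies to every patient at both V1 and V2.

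In size, it affects one of four band components in one of three secondary EEG expectations. The theta, alpha and beta components, alpha asymmetry, alpha/beta connectivity and the EAT-26 outcome are untouched.

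The conclusion rests on reading delta as the range below the article's own lower theta limit. It does not depend on the Butterworth assumption, which was used only to check that roll-off would not rescue delta. The inconsistency should be corrected, but it does not threaten the trial's main conclusion.

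**What to change.** Reconcile Measures, VII with Secondary outcome measures before EEG processing. First establish two facts that the article does not state: whether unfiltered recordings are kept, and whether the amplifier passes frequencies below 4 Hz.

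- **If both are so:** lower the offline high-pass (0.5–1 Hz is an example, not a figure from the article), add a pre-set delta band up to 4 Hz, and state whether delta enters the relative-amplitude denominator. No new recordings are needed. The cost is re-export of any files already processed, plus more slow-drift and eye-movement artefact to clean. ASR and ICA are already planned, but the article does not show how well they would cope with that added load.
- **If either is not so:** remove delta from the first EEG expectation and state that relative amplitudes and dominant frequency refer to 4–45 Hz only. The cost is a change of wording and the loss of the delta prediction.
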